#### Credibility and expectancy questionnaire

The credibility and expectancy questionnaire will be used to assess treatment expectation on a 9-point Likert scale [31]. Participants will be asked to select an answer to the following questions on their first visit (1 = “not at all”; and 5 = “somewhat”; to 9 = “very much”): “How much do you expect that *Chuna* manual therapy, usual care and combined treatment of *Chuna* with usual care will respectively alleviate your symptoms?”

### Sample size

Determination of study sample size for pCRN: the following assumptions were made for calculation of valid sample size based on previous literature: (1) level of significance (*α*) = 0.05, (2) type 2 error (*β*) = 0.2; with test power set at 80% and (3) referring to NRS difference from prior Korean medicine research using the NRS as the primary measure [32, 33], and average difference and standard deviation (SD) between the three groups specified as 1.5 and 2.5, respectively, by a designated statistician, (4) compliance was set as 80%.

G*Power 3.1.7 was used for sample size calculation, and based on (3) and applied values of mean ± SD, the derived effect size was 0.49. Consequent sample size, as determined by (1) and (2), and applying acquired sample size, was 45 (15 per group).

These results imply that to test the above hypotheses and factoring in a dropout rate of 25%, each group requires a minimum 15 × 100/75 ≒ 20 (subjects), resulting in a total 60 participants.

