### Statistical analysis

Intention-to-treat (ITT) analysis will be the primary analysis used for all subjects who receive one or more treatment sessions, and additional per-protocol analysis will be performed in subjects who complete clinical trial participation, excluding dropouts. The primary endpoint will be at 1 week following the end of treatment (7 weeks post random allocation). Continuous data will be analyzed with a paired *t* test for pre-post within-group difference and with an independent *t* test for group comparison between *Chuna* and usual care if normally distributed, and the Wilcoxon rank sum test if not. For comparing between the three groups of *Chuna* with usual care, *Chuna*, and usual care, if continuous data satisfies the normality test, analysis of variance (ANOVA) will be used to test between-group difference, and the Kruskal-Wallis test if it does not. *Chuna* with usual care versus *Chuna*, and *Chuna* with usual care versus usual care will be analyzed using Duncan’s post-hoc test. Post-hoc analysis of non-normally distributed data will use the Wilcoxon rank sum test with significance level adjusted by the Bonferroni test. Categorical data will be analyzed using the chi-square test or Fisher’s exact test. A paired *t* test will be used in pre-post within-group differences by time point. Secondary analyses will include analysis of covariance (ANCOVA) adjusting for statistically significant between-group differences in baseline outcomes or covariant factors at baseline, and subgroup analyses by LBP disease differentiation (nonspecific LBP, lumbar intervertebral disc herniation, and spinal stenosis), pain duration (subacute, chronic, and hyperchronic), and main site of pain (LBP worse than leg pain, and LBP less than leg pain) to explore the feasibility of a large, multicenter, pragmatic RCT.

All statistical analysis will use a two-tailed test as a principle, and significance level will be set at 5%. In addition, last observation carried forward (LOCF) will be conducted to handle missing data as it is currently widely used in clinical trials.

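### The 80% power fits a three-group F test with a 3-point spread of means; a pairwise difference of 1.5 points has only about 35% to 46% power

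*Protocol article*

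**What the plan says.** Sample size lists "level of significance (*α*) = 0.05", "with test power set at 80"%, and "average difference and standard deviation (SD) between the three groups specified as 1.5 and 2.5, respectively". It then reports that "the derived effect size was 0.49", obtained in G*Power, and derives 45 patients, 15 per group. The link to the study's aims is explicit: "These results imply that to test the above hypotheses and factoring in a dropout rate of 25"%, 20 per group and 60 in total are required. The section names neither the test behind the calculation nor the three group means.

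Objectives states two hypotheses. The first is that Chuna is more effective than usual care (with a safety clause). The second is that the combination is more effective than Chuna alone or usual care alone. Both are statements about pairs of arms.

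Statistical analysis plans an "independent *t* test for group comparison between *Chuna* and usual care if normally distributed", an ANOVA across the three groups, and Duncan's post-hoc test for the combined arm against each single treatment. On error rates: "All statistical analysis will use a two-tailed test as a principle, and significance level will be set at 5"%.

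**The concern.** An effect size of 0.49 is not 1.5/2.5, which is 0.60. It behaves like Cohen's f, the effect size for a three-group F test. If so, the 80% is the chance that the F test rejects equality of all three means. Rejecting that null establishes neither hypothesis, because each needs a particular arm to beat another. The total of 45 also implies a wider spread of means than the 1.5 points that a reader sees in the text.

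What is at stake is how the results are read. Someone who takes the section at its word will think that each hypothesized comparison had an 80% chance of detecting 1.5 points, and will give a non-significant Chuna versus usual care result more weight than it can bear. The pilot is also meant to inform the sample size of the full-scale trial, so a mismatch between the calculation and the hypotheses could be carried forward.

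**Working it through.** **Inputs.** From Sample size: alpha 0.05, power 80%, difference 1.5, SD 2.5, effect size 0.49, 15 per group (45), 25% dropout, 20 per group (60). From Statistical analysis: two-sided tests at 5%. From Trial design and study setting: 1:1:1 allocation.

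**1. Reproducing the plan's figure.** Cohen's f = (SD of the group means, divisor 3) / (within-group SD).
- Means 0, 1.5, 3.0: SD of means = √[(1.5² + 0 + 1.5²)/3] = 1.2247, so f = 1.2247/2.5 = 0.490.
- Omnibus F test, 2 and N − 3 degrees of freedom, noncentrality λ = f²N. N = 42: power 78.6%. N = 45: λ = 10.8, power 81.7%. N = 60: λ = 14.4, power 92.2%.
- The smallest equal group size that reaches 80% is 15, as stated, and 15/0.75 = 20 per group gives 60.

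The arithmetic is therefore sound for an omnibus F test. A two-sample t test does not give 15 per group: d = 0.60 needs 45 per arm and d = 0.49 needs 67.

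**2. Other readings of the 1.5 points (omnibus power).**

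| Reading | Means | f | N = 45 | N = 60 |
|---|---|---|---|---|
| Step between successive arms | 0/1.5/3.0 | 0.490 | 81.7% | 92.2% |
| Average of the three pairwise gaps | 0/1.125/2.25 | 0.367 | 55.7% | 69.9% |
| Full range, two arms equal | 0/0/1.5 | 0.283 | 35.5% | 46.5% |
| Full range, evenly spaced | 0/0.75/1.5 | 0.245 | 27.5% | 36.1% |

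Of these, only the first returns the stated 0.49.

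**3. Pairwise power.** Two-sample t test, two-sided 5%, SE = 2.5 × √(2/n), noncentrality = difference/SE, 2n − 2 degrees of freedom.

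| | n = 15 per arm | n = 20 per arm |
|---|---|---|
| SE | 0.913 | 0.791 |
| Power, 1.5-point pair | 35.5% | 45.6% |
| Power, 3.0-point pair | 88.7% | 95.9% |
| Difference detectable with 80% power | 2.65 | 2.27 |
| 95% CI half-width (t × SE) | 2.048 × 0.913 = 1.87 | 2.024 × 0.791 = 1.60 |

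Under Duncan's test, a 1.5-point pair has 32% to 36% power at 15 per arm and 42% to 46% at 20, depending on whether the two arms are adjacent in rank.

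**4. Size needed for one 1.5-point pair.** 80% power is first reached at 45 evaluable per arm (80.4%). With the plan's own inflation that is 45/0.75 = 60 per arm, or 180 in three arms. The plan has 45 evaluable in total.

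**The case against.** Four points can fairly be made for the plan.

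- **An omnibus ANOVA is planned.** Sizing on it matches a test in Statistical analysis, and the calculation reproduces. This stands: there is no arithmetic error. But the section ties the size to the hypotheses, and those are pairwise.
- **Not every pair is weak.** Under 0/1.5/3.0 the extreme pair has 88.7% power at 15 per arm and 95.9% at 20. This stands. A reader might infer that neither hypothesis is adequately powered; the documents do not support that, because the second hypothesis includes combined versus usual care, which may be the extreme pair.
- **The 20-per-arm column is nearer the primary analysis.** It covers everyone with at least one session and carries the last observation forward, so it should keep close to 20 per arm. This too stands, and 46% is then the better figure for a 1.5-point pair. It is still far below 80%.
- **It is a pilot.** The Abstract, Objectives and Discussion all concede that the sample may be too small for a definite conclusion. That softens the consequence but leaves the power statement uncorrected. Objectives makes sizing and feasibility the main aims only if no conclusion is reached.

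Two stronger readings should also be set aside. One is that 0.49 can arise only from 0/1.5/3.0; means of 0/0/2.6 also give 0.490, so that pattern is the natural reading of the stated 1.5, not a certainty. The other is that "compliance was set as 80"% contradicts the 25% dropout. The article defines neither term, they may be different quantities, and the larger loss was the one used (15/0.80 rounds up to 19 per arm, against 20).

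**Conclusion.** The concern holds as a mismatch between what was calculated and what is claimed. The 80% belongs to the three-group F test under a 3-point best-to-worst spread that the article does not state. For a pair 1.5 points apart, power is about 35% with 15 evaluable per arm and 46% with 20.

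Under 0/1.5/3.0 the shortfall affects the two adjacent pairs. These include Chuna versus usual care if the combination is best and usual care worst. That ordering fits the hypotheses but is an assumption, since the article assigns no means to arms. If 1.5 points is instead the full range across arms, even the F test falls short, with 27.5% to 35.5% power at 45 patients and 36.1% to 46.5% at 60.

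The pairwise and F-test figures take SD 2.5 as correct, equal arms, and testing at 5%; the t-test figures make no multiplicity adjustment.

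**What to change.** Keep 60 participants and restate the Sample size section:

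1. Name the test used in G*Power and list the assumed group means by arm.
2. Limit the 80% power to the omnibus F test under those means. If they are 0/1.5/3.0, give 81.7% at 45 evaluable and 92.2% at 60.
3. Report pairwise power for both differences: 1.5 points (35.5% at 15 per arm, 45.6% at 20) and 3.0 points (88.7% and 95.9%).
4. Give the pairwise difference detectable with 80% power (2.65 or 2.27 points) and the expected 95% CI half-width (about 1.87 or 1.60 points).
5. Remove the statement that this size suffices to test the pairwise hypotheses.

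The cost is rewording one section. No patients are added and neither design nor analysis changes; the stated power becomes less favourable.

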### Statistical analysis

Intention-to-treat (ITT) analysis will be the primary analysis used for all subjects who receive one or more treatment sessions, and additional per-protocol analysis will be performed in subjects who complete clinical trial participation, excluding dropouts. The primary endpoint will be at 1 week following the end of treatment (7 weeks post random allocation). Continuous data will be analyzed with a paired *t* test for pre-post within-group difference and with an independent *t* test for group comparison between *Chuna* and usual care if normally distributed, and the Wilcoxon rank sum test if not. For comparing between the three groups of *Chuna* with usual care, *Chuna*, and usual care, if continuous data satisfies the normality test, analysis of variance (ANOVA) will be used to test between-group difference, and the Kruskal-Wallis test if it does not. *Chuna* with usual care versus *Chuna*, and *Chuna* with usual care versus usual care will be analyzed using Duncan’s post-hoc test. Post-hoc analysis of non-normally distributed data will use the Wilcoxon rank sum test with significance level adjusted by the Bonferroni test. Categorical data will be analyzed using the chi-square test or Fisher’s exact test. A paired *t* test will be used in pre-post within-group differences by time point. Secondary analyses will include analysis of covariance (ANCOVA) adjusting for statistically significant between-group differences in baseline outcomes or covariant factors at baseline, and subgroup analyses by LBP disease differentiation (nonspecific LBP, lumbar intervertebral disc herniation, and spinal stenosis), pain duration (subacute, chronic, and hyperchronic), and main site of pain (LBP worse than leg pain, and LBP less than leg pain) to explore the feasibility of a large, multicenter, pragmatic RCT.

All statistical analysis will use a two-tailed test as a principle, and significance level will be set at 5%. In addition, last observation carried forward (LOCF) will be conducted to handle missing data as it is currently widely used in clinical trials.

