### Trial design and study setting

This pCRN study employs a multicenter, randomized, three-armed, parallel-group design. Participants will be randomly allocated to the *Chuna* manual therapy group, a usual care group, or a combined treatment group of *Chuna* manual therapy with usual care at a ratio of 1:1:1. Participants will be recruited at four major Korean medicine hospitals in Korea (Pusan National University Korean Medicine Hospital, Kyung Hee University Korean Medicine Hospital at Gangdong, Jaseng Hospital of Korean Medicine, and Mokhuri Neck and Back Hospital) and recruitment period is anticipated to be from February to August 2016. Participants will be recruited through each hospital website and online and offline advertisements. These study sites possess the facilities, personnel, and patient recognition required for LBP patient recruitment, and further information on the study sites is available at Clinical Research Information Service (CRIS registration number: KCT0001850). Participants will receive a total 6 weeks of outpatient treatment for LBP starting from visit 2 through random allocation if deemed eligible in screening at visit 1. General management and treatment processes will adhere to predetermined clinical trial procedures.

The entire research process, design, and setting were prepared through six or more meetings of 22 pCRN members including rehabilitation experts (*n* = 14), clinical research coordinators (*n* = 4), clinical research methodologists (*n* = 2), and economic evaluation experts (*n* = 2) currently employed at six university hospitals, two spine-specialty Korean medicine hospitals, and the Korea Institute of Oriental Medicine (see Additional file 2 for trial committee organization and contributions and role).

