### Blinding

As blinding of physicians and participants to allocation of treatment groups is impossible in the current design due to dissimilarity of interventions, only outcome assessors, statistician and data analysts will be blinded. The outcome assessors will not participate in treatment and a research nurse or KMD blinded to allocation will conduct outcome assessment in a separate room after treatment and will not attempt to become knowledgeable of allocation. The patient will also be cautioned against informing the outcome assessor of treatment allocation prior to each assessment. The electronic data transferred to statistician and data analysts will not contain information on treatment allocation.

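### The primary analysis is called intention-to-treat but leaves out randomised participants who never attend a session, and no stated analysis covers everyone randomised

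*Protocol article*

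**What the plan says.** The Statistical analysis section of the protocol article defines two analysis sets. The primary one is given as: "Intention-to-treat (ITT) analysis will be the primary analysis used for all subjects who receive one or more treatment sessions". The other is described as follows: "additional per-protocol analysis will be performed in subjects who complete clinical trial participation, excluding dropouts". No third set is named.

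On knowledge of treatment, the Blinding section states that "blinding of physicians and participants to allocation of treatment groups is impossible in the current design due to dissimilarity of interventions". On timing, the Trial design and study setting section describes six weeks of outpatient treatment "starting from visit 2 through random allocation if deemed eligible in screening at visit 1". Table 1 puts randomised allocation at week 0 and the first treatment in week 1.

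For missing values, the Statistical analysis section says that "last observation carried forward (LOCF) will be conducted to handle missing data". Table 1 schedules the low back pain NRS at screening and at week 0, so a pre-treatment score should exist for every randomised participant. The primary endpoint is the NRS at week 7.

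**The concern.** An intention-to-treat set consists of everyone randomised, analysed in the arm allocated. The set defined here depends on something that happens after randomisation, namely attending at least one session. It is a modified intention-to-treat set under an intention-to-treat label.

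A treated-only set does little harm when nobody knows the allocation before treatment starts, because failure to start then cannot depend on the arm. That protection is absent here: participants learn their arm before the first session. If the arms differ in who never starts, the groups compared at week 7 are no longer quite the groups that randomisation formed. With no all-randomised analysis stated, a reader could not see whether it mattered. Non-starting by arm is also information that a feasibility study needs.

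**Working it through.** **1. Can a randomised participant fall outside every stated set?**
- Allocation is at week 0 and treatment begins in week 1 (Table 1), so a participant can be randomised with no session received.
- That participant fails the entry rule of the primary set and, as a dropout, also fails the per-protocol rule.
- A participant who attends once and then leaves meets the entry rule and stays in the primary set, with missing values filled by LOCF.

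The gap is therefore confined to zero-session participants, but for them it is complete.

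**2. Arm size.** The Sample size section gives a difference of 1.5, an SD of 2.5, an effect size of 0.49, 45 evaluable participants (15 per group) and 25% dropout. These figures reproduce:
- Three equally spaced means of 0, 1.5 and 3 (the spacing is my assumption) have an SD of √[(1.5² + 0 + 1.5²)/3] = 1.2247. Dividing by 2.5 gives f = 0.4899.
- One-way ANOVA power at a two-sided 5% level is 0.786 with 42 participants and 0.817 with 45.
- 15/0.75 = 20 per group, 60 in total.

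Each arm therefore has 20 participants, and each exclusion is 1/20 = 5% of it.

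**3. Size of the shift.** Let x of the 20 in one arm never start, and let D be the difference in mean week-7 NRS between them and the rest of that arm.
- Mean of the full arm = (1 − x/20) × mean of starters + (x/20) × mean of non-starters.
- Mean in the treated-only set = mean of starters.
- The two differ by (x/20) × D.

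The protocol gives neither x nor D. Both are assumed below. Percentages are of the planned 1.5-point difference.

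| Non-starters in one arm | D = 1.5 | D = 2.5 |
|---|---|---|
| 1 | 0.075 (5%) | 0.125 (8%) |
| 2 | 0.150 (10%) | 0.250 (17%) |
| 3 | 0.225 (15%) | 0.375 (25%) |
| 4 | 0.300 (20%) | 0.500 (33%) |

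The comparison between two arms moves by this full amount only if the other arm has no such loss. Equal losses with equal D in both arms cancel.

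**4. What LOCF would do.** A participant who never starts and is not seen again has only the screening and week-0 NRS. Carrying the last value forward sets week 7 equal to baseline, which assumes no change over seven weeks. Redefining the set alone would therefore replace an exclusion with an imputed no-change score unless real week-7 values are obtained.

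**The case against.** The strongest reply is that few people, perhaps none, will be affected. Allocation and the start of treatment are both tied to visit 2, so the interval in which someone can leave may be short. Participants consent before randomisation, knowing that they may receive any of the three treatments. This is a 60-patient pilot, and the entry rule is openly stated. These points stand, and they limit the likely size of the problem. They do not make the label right or supply an analysis of everyone randomised. Pilot status is only a partial answer, because the Objectives section states comparative effectiveness hypotheses and the Sample size section justifies the numbers by a test of them.

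A reader might infer more than the text supports in three ways.

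- **That usual care would be represented only by people content with it.** This does not follow. A dissatisfied participant who attends one session remains in the primary set.
- **That the bias has a known direction, with usual care the disappointing arm.** Recruitment through Korean medicine hospitals makes this conceivable, but the protocol reports no preferences and no early refusals by arm.
- **That a third of the planned effect is at risk.** The 0.50-point figure is the extreme corner. It needs four non-starters in a single arm, which is 80% of the dropout allowance of 5 in 20, all before treatment, and a difference equal to the full planning SD of 2.5.

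**Conclusion.** The point holds. The primary set is wrong for its label, and no stated analysis includes all randomised participants. Because allocation is known before the first session, exclusion can depend on the arm. The article fixes this rule explicitly, so it is not a detail left to a fuller document.

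The size is uncertain and may be small. One non-starter differing by 1.5 points moves an arm mean by about 0.08 NRS points, and four differing by 2.5 points move it by 0.50. The number, the difference and the concentration in one arm are all assumptions. If everyone starts treatment, the two definitions coincide and nothing is lost by correcting the text. It would go too far to say that the protection of randomisation is certainly lost, since that depends on zero-session participants occurring. This should be fixed, but it does not undermine the trial.

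**What to change.** - Define the primary intention-to-treat set as all randomised participants, analysed in the arm allocated, whether or not they received a session.
- Seek the week-7 NRS from those who never start, and report their number by arm. Observed values are the real remedy, since imputing from the baseline score alone says little about their week-7 pain.
- State how week-7 values that are still missing will be handled, and add a sensitivity analysis to that method. LOCF would only carry the baseline score forward for these participants.
- Keep the treated-only set as a sensitivity analysis, named modified intention-to-treat.

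The definition can be corrected independently of the missing-data method and takes a sentence. The sample size stays at 60. The added work is the follow-up of non-starters and the stated handling of values that remain missing. The small downside is that a few more missing outcomes enter the primary analysis.

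### The combined-arm contrasts rest on Duncan's test with no stated ANOVA gate: false-positive risk is about 7.5% for hypothesis 2 if ungated, and 7.5% to 10.5% across all three contrasts

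*Protocol article*

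**What the plan says.** The Objectives section numbers two hypotheses: (1) Chuna is more effective than usual care; (2) the combined treatment is more effective than either treatment alone. Between them they cover all three pairwise contrasts. The primary endpoint is the NRS of low back pain at week 7.

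The Statistical analysis section fixes a test for each contrast:

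- Chuna versus usual care: "independent *t* test for group comparison between *Chuna* and usual care if normally distributed", otherwise a Wilcoxon rank sum test. No adjustment is given in either case.
- All three groups together: ANOVA, or Kruskal-Wallis if normality fails.
- The two combined-arm contrasts, normal data: "will be analyzed using Duncan’s post-hoc test".
- Non-normal data: "Post-hoc analysis of non-normally distributed data will use the Wilcoxon rank sum test with significance level adjusted by the Bonferroni test".

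The level is given once, for everything: "All statistical analysis will use a two-tailed test as a principle, and significance level will be set at 5" per cent. The section names no leading contrast, order of testing or division of the error rate. No sentence makes a pairwise test conditional on the ANOVA or the Kruskal-Wallis test.

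**The concern.** Duncan's multiple range test is a lenient post-hoc procedure. It holds 5% for two adjacent means but lets the level rise with the number of means spanned, so with three arms its protection is looser than the 5% used elsewhere in the plan. An overall F test in front of it would repair this, but the protocol leaves that gate to be guessed from the term post-hoc. The Chuna versus usual care t test stands outside any such gate on either reading.

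The Sample size section says the trial is sized to test the stated hypotheses. The Objectives section makes sample-size estimation and feasibility the main aims only if no definite conclusion is reached. A significant combined-arm contrast could therefore be reported as a conclusion, and its error rate would depend on an unstated choice by the analyst.

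**Working it through.** **Inputs.** From Sample size: "level of significance (*α*) = 0.05"; "with test power set at 80" per cent; "average difference and standard deviation (SD) between the three groups specified as 1.5 and 2.5, respectively"; "the derived effect size was 0.49"; 15 evaluable patients per group, 20 after allowing for 25% dropout. From Trial design: 1:1:1 allocation. From Statistical analysis: the tests listed above.

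**The plan's own figure.** An effect size of 0.49 follows if the three means are 0, 1.5 and 3 with SD 2.5: √[(1.5² + 0 + 1.5²)/3] / 2.5 = 1.225 / 2.5 = 0.49. The spacing is inferred; the article does not give it. A one-way ANOVA with f = 0.49 at 5% needs N = 45 (power 81.8%), and 15 × 100/75 = 20 per group. The stated sample size is reproduced, and it was computed for the overall three-group test.

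**Duncan's nominal level.** For a span of p means the protection level is 0.95^(p−1). With p = 3, 1 − 0.95² = 9.75%.

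**Simulated error rates.** Normal data, all three arms equal. Duncan's test used the studentized range at 0.95 for adjacent means and 0.95² for a span of three. The three-contrast rows come from 300,000 trials per setting; the hypothesis 2 gated figure comes from a separate run of 100,000.

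| At least one false positive among | Procedure | 15 per arm | 20 per arm |
|---|---|---|---|
| Chuna vs usual care only | t test | 5.0% | 5.0% |
| Two combined-arm contrasts (hypothesis 2) | Duncan, ungated | 7.4% | 7.4% |
| Two combined-arm contrasts (hypothesis 2) | Duncan after significant ANOVA | – | 4.2% |
| All three | t test plus ungated Duncan | 10.5% | 10.6% |
| All three | t test plus gated Duncan | 7.5% | 7.5% |
| All three | every contrast behind the F test | 4.9% | 5.0% |
| All three | Tukey | 4.9% | 5.0% |

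Further runs put ungated Duncan for hypothesis 2 at 7.5%, the rounded figure used in the text.

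**Gated Duncan is the same as gated pooled t tests here.** With three equal arms, F cannot exceed q²/3, where q is the studentized range of the observed means. A significant F at 20 per arm (critical value about 3.16) therefore forces q ≥ √(3 × 3.16) = 3.08, above Duncan's three-mean critical value of about 2.98. At 15 per arm the figures are √(3 × 3.22) = 3.11 against about 3.00. Once F is significant, the widest pair passes automatically and the other pairs face the ordinary pooled t criterion. The 4.2% therefore applies equally to the procedure proposed under the fix.

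**Partial nulls.** If both combined-arm contrasts are null, all three arms are equal and the F test holds 5%. If only one is null, only that one test can err, at 5%. The gate thus protects hypothesis 2 in every configuration.

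**Non-normal branch.** An unadjusted Wilcoxon test for Chuna versus usual care, plus Bonferroni-adjusted Wilcoxon tests for the other two, gives about 6.2% to 8.1% across all three contrasts, depending on sample size, the Bonferroni divisor and whether Kruskal-Wallis is a gate. For hypothesis 2 alone, Bonferroni bounds the error at 2 × 2.5% = 5%.

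**The case against.** **The protocol breaks no promise.** A reader might infer that the trial runs at twice its stated error rate. The documents do not support that: the 5% is a general level for each analysis, and nothing promises 5% across three contrasts or calls them jointly primary. This objection stands.

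**The two hypotheses are separate.** They are numbered separately, and the analysis follows that split. Whether distinct hypotheses in a multi-arm trial need joint adjustment is a matter of convention. Taken one at a time, hypothesis 1 holds 5%. Hypothesis 2 holds 4.2% on the gated reading, or about 1% if both contrasts must succeed. This stands, and it narrows the defect to ungated Duncan for hypothesis 2.

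**Post-hoc implies a gate.** That is the ordinary sense of the term, but no sentence says so, and the difference is 7.5% against 4.2%. This stands only in part.

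**The normality branch.** A reader might also infer that the normality test decides whether error is controlled at all. It does not. The non-normal branch leaves Chuna versus usual care unadjusted too, so across three contrasts the branches differ only in degree.

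**It is a pilot.** The article says it may not reach a definite conclusion and plans a full-scale trial. That lowers the stakes without removing them, because hypothesis testing is stated as an aim.

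**Conclusion.** The point holds as a cheap improvement. Duncan's test is a poor choice for hypothesis 2: as literally written it carries about a 7.5% chance of a false claim, and an explicit ANOVA gate would bring this to 4.2%. Across all three contrasts the risk is about 10.5% ungated and 7.5% gated, and neither distribution branch holds 5%. Whether that three-contrast figure counts as an excess depends on whether the sponsor wants 5% across both hypotheses, which the protocol does not say. The figures assume no true differences, normal data with equal variance, and 15 to 20 patients per arm.

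**What to change.** 1. Delete Duncan's test. State that the two combined-arm contrasts are tested only if the overall F test is significant at 5%, each then at 5% using the pooled error. Tukey's test is an acceptable alternative.
2. In the rank-based branch, put the same gate on Kruskal-Wallis, so that both branches follow one rule.
3. Choose and state the scope of error control:
   - **5% per numbered hypothesis.** Keep the separate Chuna versus usual care test and say that error is not held at 5% across both hypotheses.
   - **5% across all three contrasts.** Put Chuna versus usual care behind the same gate.

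Items 1 and 2 take two sentences. If Duncan's test was always meant to follow a significant ANOVA, item 1 changes no result, as shown above; otherwise the combined-arm contrasts give up some power for the lower error rate.

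The second option in item 3 is a real trade-off, because hypothesis 1 then depends on how the third arm performs. For a difference of 1.5 with SD 2.5, Chuna versus usual care loses no power if the combined arm is best by a further 1.5. If the combined arm equals Chuna or lies midway between the two, power falls from about 46% to 34–38% at 20 per arm, and from about 36% to 25–28% at 15 per arm.
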